## Abstract

**Background::**

In hyperbaric oxygen therapy (HBOT), a patient is exposed to pure oxygen in a chamber. While HBOT is a long-standing and well-established treatment for a wide variety of medical conditions, one of the main complications is middle ear barotrauma (MEB), which can lead to complaints of ear discomfort, stuffiness or fullness in the ear, and difficulties in equalizing ear pressure. The aim of this study is to evaluate the efficacy of self-acupressure in preventing and reducing the degree of MEB associated with HBOT.

**Methods::**

This is a prospective nonrandomized controlled study. A sample of 152 participants will be assigned to 2 groups in a 1:1 ratio. The participants in the control group will receive conventional Valsalva and Toynbee maneuvers, while those in the experimental group will be given additional self-acupressure therapy. The acupoints used will be TE17 (Yifeng), TE21 (Ermen), SI19 (Tinggong), and GB2 (Tinghui). The Modified Teed Classification, symptoms of MEB, and overall ear discomfort levels will be assessed. Data will be analyzed using the Chi-Squared test or *t* test.

**Objectives::**

This study aims to evaluate the efficacy of self-acupressure for preventing and reducing the degree of MEB associated with HBOT.

**Trial registration::**

ClinicalTrials.gov Identifier: NCT04311437. Registered on 17 March, 2020.

## Introduction

1

Hyperbaric oxygen therapy (HBOT) is a treatment in which a patient is exposed to pure oxygen for a period of time and under a certain pressure in a single-patient (monoplace) or multiple-patient (multiplace) chamber.^[1,2]^ For clinical purposes, the Undersea and Hyperbaric Medical Society (UHMS) indicates that pressurization should be 1.4 atmospheres absolute (ATA) or higher to be effective. The pressure range between 2 and 3 ATA is normally used for therapeutic purposes.^[3]^ In a monoplace chamber, only 1 patient breathes in directly pressurized 100% oxygen, while in a multiplace chamber, several patients can breathe pressurized 100% oxygen indirectly via head hood, mask, or endotracheal tube.^[4]^

HBOT is a long-standing and well-established treatment for a wide variety of medical conditions, such as musculoskeletal injuries, infections, poor wound healing, hypoxia in neurons, carbon monoxide poisoning, decompression illness, and gas embolisms.^[2,4–7]^ Although HBOT is used in numerous pathological processes and is generally safe and well tolerated, certain effects and complications may occur during the treatment,^[8]^ some examples being middle ear barotrauma (MEB), claustrophobia, oxygen toxicity, myopia, pulmonary dyspnea, and oxygen-induced seizures.^[9]^ Among all the side effects of HBOT, MEB is a common one,^[10]^ with an incidence of approximately 2%.^[9]^ However, MEB is difficult to diagnose directly. Instead, it is mostly based on patients’ subjective reports of symptoms such as ear discomfort, stuffiness or fullness in the ear, and difficulties in equalizing ear pressure.^[11]^ Once a patient exhibits clinical signs and symptoms of MEB, s/he must be evaluated via otoscopic examination to diagnose and classify the extent of the injury. Only with proper grading of MEB can medical staff decide whether treatment is required or not. Treatments can take the form of enhanced equalization education, medical intervention, or surgical intervention such as myringotomy and ventilation tube placement. Currently, MEB is evaluated and graded with 3 methods: the Teed, Modified Teed, and O’Neill grading systems.^[12]^ It is hard to predict which patients may have difficulty equalizing middle ear pressure during actual hyperbaric exposure. In clinical practice, several methods are proposed to prevent MEB associated with HBOT. These include the Valsalva and Toynbee maneuvers to open the Eustachian tubes and facilitate pressure equalization,^[13]^ nasal decongestants to reduce hyperemia and edema of the middle ear mucosal lining,^[14]^ and prophylactic myringotomy or tympanostomy tube placement.^[15]^ To the best of the authors’ knowledge, no significant studies published to date have evaluated MEB prevention methods during clinical hyperbaric exposures.

Acupuncture is a technique in traditional Chinese medicine (TCM) that was originally thought to work on the principle of redistribution of Qi, the life energy.^[16]^ In TCM theory, disease is believed to originate from an imbalance or poor flow of Qi.^[16]^ A treatment that is related to acupuncture, acupressure, is a form of touch therapy that utilizes the principles of acupuncture and Chinese medicine.^[16,17]^ In acupressure, the same anatomic locations are used as in acupuncture, but they are stimulated with finger pressure instead of needle insertion. As opposed to acupuncture, acupressure is noninvasive, simple, and typically painless. Additionally, adverse reactions caused by the insertion of fine needles can be avoided. Self-acupressure is acupressure performed by trained participants without treatment by practitioners or healthcare providers. Self-acupressure can be administered in any situation, regardless of time and place, and self-treatment can be conducted without expensive costs. Currently, several systemic reviews have reported positive effects of self-acupressure for symptom management, including symptoms of constipation, allergic diseases, nausea, vomiting, pain, stress, and sleep disturbance.^[17–20]^ So far, no research on acupressure for HBOT-related MEB has been conducted. Therefore, the aim of this study is to evaluate the efficacy of self-acupressure for preventing and reducing the degree of MEB associated with HBO.

## Methods/design

2

### Ethics approval

2.1

This protocol has been reviewed and approved by the Institutional Review Board of the Chang Gung Medical Foundation (IRB no. 201901443B0; version 3 on October 21, 2019). The protocol identification number at https://clinicaltrials.gov is NCT04311437. This study will be conducted in accordance with the principles of the Declaration of Helsinki. Before participation, all patients will receive both verbal and written forms of detailed information about the trial from physicians of the HBOT center at Kaohsiung Chang Gung Memorial Hospital (KCGMH). All participants will voluntarily sign informed consent forms that have been approved by the ethics committee prior to enrollment. Personal information about potential and enrolled participants will be collected, shared, and maintained in an independent closet to ensure confidentiality before, during, and after the trial. We will present the results and submit them for publication in peer-reviewed journals. [name] and [name] will have access to the final trial dataset, as well as disclosure of contractual agreements that limit such access for investigators.

### Study design

2.2

This prospective nonrandomized controlled trial began at the HBOT center at KCGMH in southern Taiwan in March 2020 and will continue through February 2022. The recruited participants will be assigned to the experimental group (conventional Valsalva and Toynbee maneuvers plus self-acupressure therapy, n = 76, expected) or the control group (conventional Valsalva and Toynbee maneuvers, n = 76, expected). All participants will receive education on the Valsalva and Toynbee maneuvers before the first HBOT. Participants in the experimental group will receive additional self-acupressure education from the same trained practitioner before the first HBOT. Because participants could learn the technique of self-acupressure from each other while receiving HBOT in the same chamber, the participants in the experimental and control groups will be recruited separately in different time periods. The study design has been written in accordance with the Consolidated Standards of Reporting Trials (CONSORT) 2010 guidelines.^[21]^ The overall schematic chart is provided in Figure 1.

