### Participants

2.3

The source of participant recruitment is the HBOT center at KCGMH. Physicians at the HBOT center provide information about this study to participants and then assess the participants’ eligibility to participate in it. Participants who agree to participate in the trial will provide written consent after receiving an oral explanation of the objectives and procedures of the study from their physicians.

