#### Exclusion criteria

2.3.2

Subjects will be excluded if they meet any of the following criteria:

1.pregnancy;2.acute disorders of the ears or upper respiratory tract;3.evidence of neurologic dysfunction precluding them from making an informed decision;4.tracheostomy or endotracheal intubation;5.myringotomy, tympanoplasty, mastoidectomy, or tympanostomy tube placement.

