### Interventions

2.5

All participants will receive education from trained practitioners on the Valsalva and Toynbee maneuvers before the first HBOT. The participants in the experimental group will undergo additional education and training in self-acupressure therapy. The acupoints used will be TE17 (Yifeng), TE21 (Ermen), SI19 (Tinggong), and GB2 (Tinghui) (Fig. 2). All acupoints have been selected and localized according to the WHO Standardized Acupuncture Point Location guidelines.^[23]^ The education on self-acupressure therapy will be provided by the same trained practitioner, who has received sufficient training from a licensed TCM doctor in Taiwan. The self-acupressure therapy protocol is as follows: In a sitting position, the patient applies firm pressure (3–5 kg of pressure) with the fingertips in a circular motion at a speed of 2 circles per second for a duration of one minute per acupoint, with 1 to 2 seconds of rest after each 10 circles. The complete process lasts for about 5 minutes. A weighing scale is used for calibrating the correct amount of finger pressure necessary for the acupressure treatment. The participants in the control group will receive routine Valsalva and Toynbee maneuvers before the first HBOT, without additional education on self-acupressure.

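### Each arm has its own recruitment period, so the arm is foreseeable when physicians screen and consent patients, and who is enrolled can depend on it

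*Protocol article*

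**What the plan says.** Section 2.2 of the protocol article describes the design openly: "This prospective nonrandomized controlled trial began at the HBOT center at KCGMH". The rule that decides the arm is the recruitment period, since "the participants in the experimental and control groups will be recruited separately in different time periods". The reason given is contamination: "Because participants could learn the technique of self-acupressure from each other while receiving HBOT in the same chamber". The Discussion repeats both the rule and the reason.

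Section 2.3 sets out who admits patients and in what order. "Physicians at the HBOT center provide information about this study to participants and then assess the participants’ eligibility to participate in it", and consent comes "after receiving an oral explanation of the objectives and procedures of the study from their physicians". Section 2.1 also has the centre's physicians inform patients before enrolment.

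Among the exclusions in 2.3.2 is "acute disorders of the ears or upper respiratory tract". Acupressure training is a separate step with its own person: "The education on self-acupressure therapy will be provided by the same trained practitioner" (2.5). Baseline outcomes are taken before the first HBOT (2.6). The stated comparison is a t test or a chi-squared test (2.7).

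**The concern.** With one arm open at a time at one centre, the next patient's arm is settled before the physician meets that patient. The people who could know it are those who decide whom to approach, apply the eligibility criteria and explain the procedures at consent.

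Two of these steps involve judgement that may bear on the risk of middle ear barotrauma (MEB): whom to approach, and whether an ear or upper respiratory complaint counts as an acute disorder. Patients may also accept or decline knowing whether acupressure is on offer.

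This is not the same as calendar confounding. Suppose the two periods had identical referrals, practice and grading. The enrolled groups could still differ, because entry decisions were made with the arm foreseeable.

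If patients of different MEB risk enter the two arms, the Modified Teed comparison and the discomfort scores mix selection with any acupressure effect. A clinical impression of ear risk or a patient's enthusiasm for acupressure may never be written down, and covariate adjustment cannot recover what was not recorded.

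**Working it through.** **Step 1: does the text support the premise?** Put 2.2 beside 2.3. Section 2.2 gives one centre with one arm open per period. Section 2.3 has that centre's physicians inform, screen and consent. The article does not say outright that they know the current arm, but period-wise recruitment makes it foreseeable whatever the order or dates of the periods. The supported statement is that they can know it, and that enrolment can depend on it.

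**Step 2: the plan's own figure.** Inputs from 2.4: 10.8% against 0.0%, 80% power, alpha 0.05 (taken as two-sided), 10% dropout. With the pooled-variance formula and a mean rate of 0.054:

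n = [1.96·√(2·0.054·0.946) + 0.842·√(0.108·0.892)]² / 0.108² = 67.6, so 68 per group.

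68 / 0.9 = 75.6, so 76. The stated 76 per group reproduces, with 68 evaluable.

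**Step 3: an illustration of size.** Only the 10.8% and the 68 come from the plan. The rest is assumed:

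- no acupressure effect, and 10.8% risk in the control group;
- a share q of eligible patients (0.2 or 0.3) at higher risk, with relative risk RR (3 or 5);
- a fraction s of those higher-risk patients not enrolled in the acupressure period, with everyone enrolled in the control period.

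Low-risk rate: b = 0.108 / (1 − q + q·RR).

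Higher-risk share in the acupressure group: q′ = q(1 − s) / [q(1 − s) + 1 − q].

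Acupressure-group rate: b(1 − q′ + q′·RR).

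Example with q = 0.3, RR = 5, s = 0.5: b = 0.108/2.2 = 0.0491; q′ = 0.15/0.85 = 0.176; rate = 0.0491 × (0.824 + 0.882) = 0.0837. The spurious benefit is 10.8 − 8.37 = 2.43 percentage points.

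The chance of a significant result favouring acupressure (two-sided 0.05, 68 per group) comes from summing exact binomial probabilities over all pairs of event counts. Ranges are over the four combinations of q and RR:

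| s | Acupressure-group rate | Spurious benefit (points) | False benefit, uncorrected chi-squared | With continuity correction |
|---|---|---|---|---|
| 0 | 10.8% | 0 | 2.5% | 1.3% |
| 0.25 | 10.15% to 9.69% | 0.65 to 1.11 | 3.3% to 4.1% | 1.7% to 2.1% |
| 0.50 | 9.43% to 8.37% | 1.37 to 2.43 | 4.5% to 7.0% | 2.4% to 3.7% |
| 0.75 | 8.62% to 6.81% | 2.18 to 3.99 | 6.3% to 12.8% | 3.4% to 7.1% |

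For s of 0.25 to 0.50, the spurious benefit is 6% to 22% of the 10.8-point planning difference (0.65/10.8 to 2.43/10.8). The highest value, 12.8%, is one corner: q = 0.3, RR = 5, s = 0.75.

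**The case against.** **The design is declared non-randomized, with a reason.** That is true, and the reason justifies separate periods. It does not require that entry decisions and baseline readings be made with the arm in view, so the selection risk remains.

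**The protocol itself limits how strong selection could be.** The Introduction says that trouble with equalizing is difficult to foresee, and patients enter at their first HBOT, so no earlier course has revealed it. This stands. Screening out 75% of higher-risk patients would need more foresight than the protocol allows, so the 12.8% should not be read as an expected error rate.

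**The rate is borrowed.** The 10.8% is moderate to severe otalgia in an earlier study, not a Modified Teed rate. Section 2.7 does not say whether the chi-squared test is continuity-corrected, and the corrected figures are roughly half as large. This also stands: the table illustrates the risk and estimates nothing about the primary outcome.

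**The full protocol may already contain a screening log or consecutive enrolment.** A reader might infer from the article's silence that these are missing. The article is a condensed account and its flowchart is not shown, so that inference is not supported. The point rests on the stated allocation rule and entry sequence.

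**An arm-aware baseline score matters little.** Largely true, since 2.7 names no baseline adjustment. Taking baseline readings earlier is worthwhile mainly because it documents comparability.

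**Conclusion.** The point holds as a weakness of the stated design. The arm is foreseeable at entry, the people who screen and consent can know it, and unrecorded selection cannot be adjusted away. It arises from the same sentence as calendar confounding but is a different mechanism.

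Its size and direction are unknown. Under assumed selection of 25% to 50%, the chance of a falsely significant benefit is about 3% to 7% against 2.5%, subject to the stand-in rate and the uncorrected test. Selection in the opposite direction would hide a real benefit.

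A reader might infer that physicians did select patients, or that a positive result would be an artefact. The documents show neither; they show only that the entry process does not rule selection out. Because the Discussion expects the trial to supply evidence of efficacy, this should be addressed, with medium confidence in its practical importance.

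**What to change.** Keep the separate periods. In 2.3, require for both periods that:

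1. every consecutive patient prescribed a first HBOT is approached;
2. eligibility, including the ear and upper respiratory exclusion, and the baseline Modified Teed and VAS readings are recorded before any arm-specific information or education is given;
3. everyone screened is logged, with the reason for any non-enrolment.

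Report enrolment fractions and baseline ear findings by arm, and state in the conclusion that allocation was not concealed. If recruitment is already advanced, apply this to the remainder.

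Two apparently stronger remedies are not advised. Several periods of random length would make the next switch harder to foresee. However, follow-up runs to the twentieth HBOT, so each switch would put both arms in the chamber together unless recruitment paused. A single consent form describing acupressure to control patients would invite the contamination that the design tries to avoid.

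The cost is a short amendment, a screening log and slightly more work at entry, with no additional patients. Physicians may still infer the current arm, so the bias is reduced and made visible but not removed.

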**Figure 1 F1:**
[figure not shown]
The flowchart of the trial.

### Participants

2.3

The source of participant recruitment is the HBOT center at KCGMH. Physicians at the HBOT center provide information about this study to participants and then assess the participants’ eligibility to participate in it. Participants who agree to participate in the trial will provide written consent after receiving an oral explanation of the objectives and procedures of the study from their physicians.

#### Inclusion criteria

2.3.1

Subjects are eligible to participate if they meet all the following criteria:

1.age of 20 years or older;2.clear consciousness and ability to communicate;3.prescription to receive first HBOT;4.consent to participate in the study.

#### Exclusion criteria

2.3.2

Subjects will be excluded if they meet any of the following criteria:

1.pregnancy;2.acute disorders of the ears or upper respiratory tract;3.evidence of neurologic dysfunction precluding them from making an informed decision;4.tracheostomy or endotracheal intubation;5.myringotomy, tympanoplasty, mastoidectomy, or tympanostomy tube placement.

#### Dropout criteria

2.3.3

Participants will be dropped from the trial under the following conditions:

1.unstable vital signs and need for first aid during study period;2.deterioration in clinical condition leading to an assessment by medical staff of unsuitability to continue the study;3.participant's decision to withdraw from the trial at any time.

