### Outcome measurements

2.6

The primary outcome measurement is the presentation of the tympanic membrane recorded according to the Modified Teed Classification, with grades from 0 to 5, where Grade 0 indicates symptoms with no ontological signs of trauma; Grade 1 indicates injection of the tympanic membrane; Grade 2 indicates Grade 1 plus injection plus mild hemorrhage within the tympanic membrane; Grade 3 indicates gross hemorrhage within the tympanic membrane; Grade 4 indicates free blood in the middle ear, evidenced by blueness and bulging; and Grade 5 indicates perforation of the tympanic membrane.

The secondary outcomes are symptoms of MEB and the overall ear discomfort levels. Recorded symptoms of MEB include feeling pressure in the ears, ear pain, headache, dizziness, vertigo, tinnitus, and hearing loss. The symptoms of MEB and the overall ear discomfort levels will be estimated using a 10-cm visual analogue scale with anchor points of 0 (no discomfort) and 10 (maximum discomfort) at the same time as the primary outcome measure. A higher score will indicate a higher level of discomfort during HBOT. The outcomes will be measured at baseline before the first HBOT, after the first 5 consecutive treatments of HBOT, and after each 10 treatments of HBOT until the twentieth HBOT.

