## Discussion

3

MEB, one of the main common side effects of HBOT, is a major reason why patients discontinue HBOT. Although the Valsalva and Toynbee maneuvers are usually used to prevent symptoms of MEB associated with HBOT, many patients still experience ear discomfort during and after HBOT. The present study aims to evaluate whether additional self-acupressure in combination with the Valsalva and Toynbee maneuvers is more effective in preventing and reducing the discomfort caused by MEB than are the Valsalva and Toynbee maneuvers alone. Self-acupressure is a simple, noninvasive treatment that can be performed at any time, as opposed to acupuncture, which is invasive and can only be performed by trained physicians. If additional self-acupressure is proven more effective, patients may be more willing and feasible to complete the course of HBOT.

Acupressure, which originated in ancient China, is based on the theory of TCM and is closely associated with acupoint activation across the meridians, just as acupuncture is. Acupressure uses pressure to stimulate specific acupoints which can correct imbalances in the *Qi* through channels and subsequently treat diseases.^[16]^ The biochemical mechanism of acupressure involves the stimulation of acupoints that leads to complex neuro-hormonal responses, such as antiinflammation via the hypothalamic-pituitary-adrenocortical axis.^[16]^ In addition, acupressure mediates the nitric oxide signal, which is known to improve local microcirculation via cyclic guanosine monophosphate.^[16]^ Stimulation of acupoints near the ear may alleviate symptoms of MEB. In the present study, correct position and proper strength during self-acupressure will be important. One well-trained practitioner will educate the participants in the experimental group on additional self-acupressure therapy and confirm that the self-acupressure is correctly performed. The participants in the experimental group and those in the control group will be recruited in separate periods of time so as to avoid contact between the 2 groups of participants and thereby minimize the likelihood that the patients might learn about self-acupressure from one another while receiving HBOT in the same chamber.

In conclusion, the results of this study are expected to provide evidence on the efficacy of self-acupressure as a no cost, noninvasive self-management method for MEB associated with HBOT in addition to the Valsalva and Toynbee maneuvers.

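### Post-baseline outcomes are read only at fixed treatment counts with no exit reading stated, so a participant whose ears end HBOT before the fifth treatment has no post-baseline Teed grade

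*Protocol article*

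**What the plan says.** Everything here comes from the protocol article.

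- **Entry (2.3.1).** The treatment-related criterion is a "prescription to receive first HBOT". Nothing requires that five sessions be planned or completed.
- **Outcome times (2.6).** "The outcomes will be measured at baseline before the first HBOT, after the first 5 consecutive treatments of HBOT", then by treatment count up to the twentieth. The Teed grade (primary) and the VAS scores (secondary) share these times. No reading is tied to stopping HBOT, leaving the trial or the onset of symptoms.
- **Dropout (2.3.3).** "Participants will be dropped from the trial under the following conditions": besides unstable vital signs, these are "deterioration in clinical condition leading to an assessment by medical staff of unsuitability to continue the study" and the participant's "decision to withdraw from the trial at any time".
- **Link between outcome and stopping (Discussion).** MEB "is a major reason why patients discontinue HBOT".
- **Clinical background (Introduction).** Patients with signs of MEB need an otoscopic examination, and treatment can extend to "surgical intervention such as myringotomy and ventilation tube placement". This describes practice in general and does not define a trial outcome time.
- **Allowance for loss (2.4).** A 10% dropout rate is built into the 76 per group.

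**The concern.** The trial asks whether self-acupressure prevents MEB or reduces its degree. By the protocol's own account MEB makes patients stop HBOT, yet a participant must complete five consecutive treatments before the ear is first graded after baseline. Early ear trouble can therefore remove a participant from the record because of the event that the trial is meant to count.

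This is a matter of data collection, which the protocol fixes, more than of analysis. A statistical analysis plan can choose how to treat missing grades, but it cannot supply a grade that was never taken. What is at stake is the observed MEB rate in each group, the absolute difference, and the power of a comparison in which few events are expected.

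**Working it through.** **Step 1: reproduce the sample size.** Inputs from section 2.4: 10.8% against 0.0%, α = 0.05 (two-sided assumed), power 80%, dropout 10%.

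n = [1.960·√(2·p̄·(1−p̄)) + 0.842·√(p₁(1−p₁) + p₂(1−p₂))]² / (p₁−p₂)², with p̄ = 0.054

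n = [1.960·√0.1022 + 0.842·√0.0963]² / 0.108² = 0.788 / 0.01166 = 67.6, so 68 per group.

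68 / 0.9 = 75.6, so 76. The stated figure reproduces.

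**Step 2: what the 10% covers.** At 10.8%, 76 controls yield 76 × 0.108 = 8.2 expected events. Ten per cent dropout is 7.6 participants. In the extreme case that every control dropout is an MEB case, 8.2 − 7.6 = 0.6 events remain among 68.4 participants (0.9%). That is a bound, not a forecast. It shows that the allowance is almost as large as the whole expected event count.

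**Step 3: loss that depends on the outcome.** Let f be the share of MEB cases that leave before the first post-baseline reading. The documents do not give f, so a range is shown.

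Observed risk = p(1−f) / (1−pf); participants read = n(1−pf)

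For f = 0.25: 0.081 / 0.973 = 8.3%. For f = 0.5: 0.054 / 0.946 = 5.7%. The experimental rate stays at 0%. Power uses the same normal approximation as Step 1.

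| f | Observed control rate | Power from 76 per group | Power from 68 per group |
|---|---|---|---|
| 0 | 10.8% | 84.5% | 80.3% |
| 10% | 9.8% | 80.5% | 76.0% |
| 25% | 8.3% | 73.0% | 68.2% |
| 50% | 5.7% | 56.0% | 51.5% |

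The 76 column assumes no other dropout. The 68 column assumes that the planned 10% has already gone for unrelated reasons.

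The approximation is rough when one rate is zero. Exact enumeration, from 76 and 68 per group, gives:

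| f | Uncorrected chi-squared | Fisher's exact |
|---|---|---|
| 0 | 97.0% and 94.5% | 84.2% and 75.6% |
| 25% | 87.4% and 81.0% | 74.8% and 65.2% |
| 50% | 59.4% and 50.0% | 39.3% and 30.2% |

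The level depends on the method. The fall from no loss to a quarter and then to half appears in all three.

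**Step 4: which measure moves.** The observed odds are p(1−f)/(1−p), the true odds times (1−f). With the same f in both groups the factor cancels in the odds ratio. Take true risks of 20% and 10% (assumed for illustration, since a 0% arm is uninformative here) and f = 0.5:

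- Observed risks: 0.10/0.90 = 11.1% and 0.05/0.95 = 5.3%.
- Difference: 5.8 points instead of 10.
- Odds ratio: 0.444 before and after. Risk ratio: 0.50 becomes 0.474.

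With f = 0.25 the risks are 15.8% and 7.7%, a difference of 8.1 points.

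If the share differs by group, the observed odds ratio is the true one times (1−f_exp)/(1−f_ctl):

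- Half lost in control, a quarter in experimental: 0.444 × 0.75/0.50 = 0.667, so the benefit is understated.
- The reverse: 0.444 × 0.50/0.75 = 0.296, so it is overstated.

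**The case against.** The strongest reply is that this is a condensed article. An exit assessment could sit in the full protocol, and the analysis set and missing-data rules belong in an analysis plan that is not shown. The second half stands: section 2.7 names tests only, and its silence on who is analysed is no fault. The first half stands only in part. The article states the measurement times and the dropout conditions, and as stated they leave early leavers without a grade.

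Further points in the plan's favour also stand:

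- Baseline is measured, so what is lost is the post-baseline reading.
- Stopping HBOT is not a listed dropout condition. A reader might infer that everyone who stops is dropped; section 2.3.3 does not say so. Loss arises through withdrawal, through a judgement of unsuitability, or because the visits are counted in treatments.
- MEB in participants who continue is still graded if it is visible at the visit.
- The Discussion gives no discontinuation rate and does not say that stopping happens before the fifth treatment.
- The only MEB incidence given is about 2% (Introduction), and the 10.8% concerns otalgia. The power figures therefore illustrate and do not estimate.

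Two stronger readings lack support. One is that otoscopies done for symptoms between visits will be ignored; the article does not say how the trial uses them. The other is that a surgical opening made to treat MEB would be scored as Grade 5; section 2.6 defines that grade as perforation, and nothing says that a surgical opening would count as one.

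**Conclusion.** The point holds in a limited form. On the stated schedule, a participant whose ears end HBOT before the fifth treatment has no post-baseline Teed grade, and the protocol itself names MEB as a major cause of stopping. The dropout allowance does not address this.

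The size depends on an unknown share of lost cases. With an equal share in both groups and the otalgia planning rates, losing a quarter leaves about 68–73% power by the plan's own type of calculation, and losing half about 52–56%. Exact calculations give other levels and the same direction.

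A reader might infer that the comparison is necessarily biased towards hiding a benefit. The documents do not support that. With equal loss the odds ratio is preserved, and the cost is a smaller absolute difference and less power. With unequal loss the bias can run in either direction. Nor do the documents show that leavers will be excluded from the analysis. The defect is that the primary reading may never be taken.

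**What to change.** **In section 2.6**, add a Teed grade and VAS when a participant stops HBOT or leaves the trial, at the last attended session where possible, and record the reason for stopping.

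**For participants without a scheduled reading**, use the exit grade or the grade from any otoscopy already done for symptoms, in each case one taken before any ear procedure.

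**Add a sensitivity analysis** that counts stopping for ear reasons, or an ear procedure for MEB, as an MEB event. Keeping this out of the primary definition leaves the endpoint as the protocol sets it.

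**Also report the scheduled-visits-only result.** Symptom-triggered readings depend on unmasked reporting, and the groups are recruited in separate periods.

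The cost is a little extra data collection and some protocol wording. Some leavers will still be missed, because a participant who simply does not return cannot be graded at a session that nobody knew was the last. No clinical stopping rule changes.
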